### Definition of analysis population relating to protocol non-adherence and any statistical methods to handle missing data {20c}

The full analysis set (FAS) will include all patients randomized to the trial who underwent liver transplantation. This means that patients in whom liver transplantation is not completed or who did not receive a full graft will be excluded, as these patients retrospectively violate inclusion criteria. Reasons for canceling a transplantation may be that the liver graft is not accepted for transplantation or that an unexpected disease is found in the recipient.

The FAS will then be analyzed in adherence to the intention-to-treat principle, analyzing patients according to their randomized treatment.

In terms of “intercurrent events,” we are using a “composite variable strategy” regarding the intercurrent event of death by integrating death in the primary outcome tumor recurrence-free survival and a “treatment policy strategy” regarding all patients who received transplantation [40].

For the primary outcome, we only expect missing data in patients who withdraw from the trial. Their primary outcome and secondary outcomes that are components of the primary outcome will be right censored at the time of withdrawal. The remaining secondary outcomes will be analyzed by complete case analysis. Due to the expected truncation of secondary outcomes by death, especially those outcomes measured later during follow-up, multiple imputation of missing values is not planned, since this would mean imputing data beyond death. Depending on the number of deaths and their balance between study arms, principal stratification may be used to additionally estimate the survivor average causal effect.

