### Sample size {14}

The sample size was calculated to show superiority of HOPE over conventional cold storage regarding HCC recurrence-free survival (time to HCC recurrence or death). The power was set to 80% at a significance level of 5%. Based on previous studies on Liver transplantation in patients with HCC, we expect that 15% of the patients in the control arm will develop tumor recurrence or die within 24 months [2, 26–28]. Based approximately on the results of a retrospective cohort study, we expect this risk to be reduced to 5% of the patients in the HOPE arm [14]. Under the assumption of exponential survival times, these rates correspond to a hazard ratio (HR) of 0.32. We expect an accrual period of 12 months and plan a minimum follow-up duration of 24 months (resulting in a total study duration of 36 months). Based on the method of Lachin and Foulkes and as implemented in the function *nSurvival* from the R package *gsDesign*, we will need 208 patients to be able to observe 26 events [29–31]. We expect a dropout rate of 5%, similar to the dropout rate of 4% observed in Schlegel et al. [18]. We will thus need to recruit 220 patients (110 per treatment arm).

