### Implementation {16c}

The R code to create the randomization lists will be prepared at the Department of Biostatistics of the Epidemiology, Biostatistics, and Prevention Institute, University of Zurich, Switzerland. An independent person at the Department of Clinical Research Basel, who is not otherwise involved in the trial, will then specify the random seed and run the code to produce the randomization lists. The random seed will determine the allocation and ensure reproducibility of the randomization lists. The randomization lists will then be handed over to the responsible data manager at the Department of Clinical Research, University Hospital Basel, Switzerland, who will store the lists in SecuTrial®. The allocation of a liver graft will be revealed to the transplant surgeon after the donor liver is accepted for transplantation to a particular recipient and is enrolled in the trial. More precisely, after inclusion and exclusion criteria are entered in SecuTrial®, the allocation will be done by clicking a “randomize” button in SecuTrial® by a designated member of the local study team.

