## Assignment of interventions: blinding

### Who will be blinded {17a}

The allocation is blinded for all persons who perform the outcome assessments. Patients are also blinded. The statistician will be blinded for the sample size re-estimation during the interim analysis but will be unblinded for the final analysis. Surgeons are unblinded for the intervention as they are involved in the storage or perfusion process of the organs. However, the randomization result must not be listed on the surgery or any other report accessible to the study personnel not involved in the surgery to prevent unblinding.

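### The full analysis set depends on a transplantation completed after allocation is known, so it is a modified intention-to-treat set and is open to arm-dependent exclusion

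*Protocol article*

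**What the plan says.** All references are to the Protocol article.

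- **Analysis set.** The section on statistical methods {20a} runs the primary analysis on the full analysis set (FAS). The section on the analysis population {20c} defines the FAS as randomised patients who were transplanted, and adds that "patients in whom liver transplantation is not completed or who did not receive a full graft will be excluded". The reason given is that such patients turn out, in retrospect, to breach the inclusion criteria. As examples, "Reasons for canceling a transplantation may be that the liver graft is not accepted for transplantation", or an unexpected disease is found in the recipient. The same section says the set is analysed by intention to treat, with a composite strategy for death and a treatment-policy strategy for transplanted patients.
- **Timing of allocation.** Implementation {16c}: "The allocation of a liver graft will be revealed to the transplant surgeon after the donor liver is accepted for transplantation to a particular recipient", once eligibility has been entered and the patient is enrolled.
- **Blinding.** Section {17a}: "Surgeons are unblinded for the intervention as they are involved in the storage or perfusion process of the organs".
- **Primary outcome.** Outcomes {12} counts recurrence or death from any cause.
- **Eligibility.** Section {10} lists among the exclusion criteria the histology of the explanted liver, mTOR inhibitor treatment after transplantation, and cold storage above 10 h in either arm.

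**The concern.** Membership of the primary analysis set is decided by something that happens after allocation. The graft is accepted, the arm is revealed, and only then can a graft be refused or a transplantation abandoned. The people closest to that decision know the arm. If refusals or abandoned operations differ between arms and are related to prognosis, the two groups compared are no longer those that randomisation formed.

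Two further points follow.

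- If not completed is taken at its word, a death on the operating table leaves the analysis, although it is an event under the outcome definition and under the composite strategy for death.
- The stated justification does not fit well. None of the inclusion criteria in {10} requires a completed transplantation; the relevant one is being listed for it. A partial graft, and an acute unexpected contraindication, match listed exclusion criteria. A whole graft refused after acceptance matches none.

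Separately, some exclusion criteria in {10} cannot be known, or may not be settled, when the patient is randomised. The reasoning used in {20c} could be extended to those patients, and the text does not rule this out.

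**Working it through.** **1. Order of events.** {16c}: graft accepted, eligibility entered, patient randomised, arm shown to the surgeon. {20c}: patient leaves the FAS if the graft is then not accepted or the transplantation is not completed. Acceptance comes before allocation, so a refusal under {20c} comes after it.

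**2. The plan's own sample size (Sample size {14}).** Inputs: "we expect that 15% of the patients in the control arm will develop tumor recurrence or die within 24 months"; "we expect this risk to be reduced to 5% of the patients in the HOPE arm"; 12 months of accrual, 36 months in total, 80% power, 5% significance (taken as two-sided, which reproduces the plan's figure).

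- Monthly hazards: −ln(0.85)/24 = 0.00677 and −ln(0.95)/24 = 0.00214. Ratio 0.316, which agrees with "these rates correspond to a hazard ratio (HR) of 0.32".
- Event probability with uniform accrual: p = 1 − [exp(−24λ) − exp(−36λ)]/(12λ). Control 0.1836, HOPE 0.0621, at the mean hazard 0.125.
- Lachin–Foulkes on the log hazard ratio scale: N = {[1.96·√(4/0.125) + 0.842·√(2/0.1836 + 2/0.0621)]/ln 0.316}² = 207.5, so 208 patients and 25.5, so 26, events.
- 208/0.95 gives 219, or 220 as an even number.

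The design reproduces. The 5% allowance is for dropout; exclusions from the FAS are not mentioned.

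**3. Events per arm.** 104 × 0.1836 = 19.1 control; 104 × 0.0621 = 6.5 HOPE.

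**4. What selective removal could do.** The documents give no exclusion rate, so the following are assumptions: no true effect, 110 patients per arm, mean hazard in both arms equal to the control hazard above, 10% of patients at 3-fold or 5-fold hazard, and exclusions only from HOPE and only among those high-risk patients. Simulated with a log-rank test and crude event-rate ratios, not with the planned mixed-effects Cox model:

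| HOPE patients removed (about) | Median HR, 3-fold | False superiority, 3-fold | Median HR, 5-fold | False superiority, 5-fold |
|---|---|---|---|---|
| 0 | 1.00 | about 2.5% | 1.00 | about 2.5% |
| 3 | 0.96 | 3.4% | 0.94 | 3.6% |
| 6 | 0.92 | 4.0% | 0.88 | 6.0% |
| 9 | 0.89 | 5.7% | 0.82 | 8.3% |

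Exclusions of this kind from the control arm would push the other way.

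**5. What non-selective removal would do.** If exclusions are unrelated to prognosis, losing one HOPE event takes about 104/6.5 = 16 exclusions. For exclusions balanced between arms on top of 5% dropout, 220 × 0.95 × (1 − x) patients remain. Expected events are that number times the mean event probability, (0.1836 + 0.0621)/2 = 0.123. Power by Schoenfeld's formula is Φ(|ln 0.316|·√d/2 − 1.96):

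| Assumed exclusion rate x | Patients left | Events d | Power |
|---|---|---|---|
| 0 | 209 | 25.7 | 0.83 |
| 2% | 205 | 25.2 | 0.82 |
| 5% | 199 | 24.4 | 0.81 |
| 10% | 188 | 23.1 | 0.79 |

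The loss is one of precision and is small.

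**6. Criteria known only later.** {16c} requires the exclusion criteria to be entered before randomisation. {10} includes explant histology and post-transplant mTOR inhibitor use, which cannot be known then, and realised cold storage time, which may not be settled then. {20c} names only two grounds for leaving the FAS, and these are not among them.

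**The case against.** The strongest case on the other side has five parts.

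- **Late-known criteria.** A reader might infer that transplanted patients with non-HCC histology, mTOR inhibitor use or cold storage above 10 h are removed, so that the eligibility list and the FAS give two different analysis sets. The text does not say so. Read literally, {20c} keeps them under treatment policy; {11d} treats mTOR inhibitors as prohibited concomitant care and {11c} records cold storage time to identify non-adherence. A reader might also infer that the cold storage limit removes mainly controls. The limit is stated for both arms, a HOPE graft can also pass it before perfusion starts, and no removal is prescribed. What stands is an ambiguity to be closed.
- **Who decides, and why.** The protocol does not say who refuses a graft, and unexpected disease in the recipient is not evidently tied to the arm. The Discussion's remark that organs can be tested before use concerns machine perfusion in general, and {11a} sets no viability criterion for HOPE. This makes arm-dependent refusal possible, not shown.
- **Death in surgery.** It is never named as an exclusion, and the examples in {20c} are cancelled transplantations. The literal wording still covers it, so it needs a sentence.
- **Time origin.** Post-transplant survival has no natural start in a patient who is not transplanted. This is a fair reason for a modified set, and why an all-randomised analysis must run from randomisation as a sensitivity analysis.
- **Level of detail.** Exclusion tables and sensitivity sets often sit in a separate analysis plan, and their absence here is no fault. The FAS definition and its intention-to-treat label, however, are fixed in this document.

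**Conclusion.** The point holds in a limited form. The primary set is conditioned on a completed full-graft transplantation, which is decided after an unblinded surgeon has learned the arm. It is a modified intention-to-treat set, and it exposes the comparison to arm-dependent selection. On its literal wording it also drops intraoperative deaths that the outcome definition counts.

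The size is unknown, because no exclusion rate is given. The range of 0.96 to 0.82 for a true hazard ratio of 1 rests on one-sided removal of about 3 to 9 high-risk HOPE patients, which is an unfavourable case; exclusions balanced between arms and unrelated to prognosis would leave the estimate essentially intact. A reader might conclude that the trial loses the protection of randomisation altogether. The documents do not support that: they show an open route to selection and not that it is used. The sample size calculation is correct on its own inputs and is not affected.

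**What to change.** In {20c}:

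1. Call the set modified intention-to-treat.
2. Count death during transplantation surgery as a primary event at day 0 in the randomised arm, and define what not completed means.
3. Allow exclusion after allocation only for reasons judged without knowledge of the arm, and report all exclusions and reasons by arm. Blind review cannot undo a refusal that was itself made knowing the arm, so item 5 is needed as well.
4. State that transplanted patients who meet an exclusion criterion known only later stay in the FAS, under the treatment-policy strategy already named.
5. Add a sensitivity analysis of all randomised patients, timed from randomisation, using whatever follow-up is available for those not transplanted. Table 1 sets out post-transplant visits, so this follow-up may be thin.

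Sections {10}, {16c} and {20c} must be reconciled on the criteria that cannot be settled at randomisation. How the cold storage and mTOR inhibitor rules operate clinically is for the sponsor.

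The cost is wording, one sensitivity analysis and slight dilution of the effect from the patients kept in. If the eligibility text itself is changed and the change counts as substantial, {25} requires ethics committee approval first.

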Single components of the events considered for the primary outcome (tumor recurrence, HCC-related death, death from other causes) will be analyzed by cause-specific mixed-effects Cox models. We will account for competing risks by censoring patients with the competing event on the date of the competing event. We will use the Aalen-Johansen estimator to derive cumulative incidence function curves for all competing events. HMGB-1 on day 7 and circulating tumor DNA in blood at discharge and 6 months after transplantation will be analyzed by linear mixed-effects models, with corresponding measurements at baseline as covariates. The models will include a random intercept per center, and the one for circulating tumor DNA in blood will additionally contain a random intercept per patient, to account for the repeated outcome measurements. Log-transformation or a switch to a generalized linear mixed-effects model will be considered in case of violation of the normality assumption. Acute rejection index (ordinal outcome) will be compared between groups by a proportional odds model stratified by center [36]. The number of Liver-related complications experienced by the patient within 2 years will be analyzed the same way, since it is expected to be zero for a considerable proportion of the patients as in Schlegel et al. and thus analysis as a count is complicated [37]. As for the primary outcome, we will report effect sizes with 95% CI and *p* values for all secondary outcomes.

No statistical tests will be performed for other outcomes, but they will be descriptively compared between treatment arms.

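### The reason for complete case analysis of ctDNA, HMGB-1 and the Rejection Activity Index covers only patients who died; missing baseline samples discard observed outcomes, and a ctDNA case is undefined

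*Protocol article*

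**What the plan says.** Section {20c} of the Protocol article right-censors the primary outcome and its components at withdrawal. For the other secondary outcomes it states: "The remaining secondary outcomes will be analyzed by complete case analysis". The reason against imputation is given in one sentence. It opens "Due to the expected truncation of secondary outcomes by death, especially those outcomes measured later during follow-up" and concludes that "multiple imputation of missing values is not planned, since this would mean imputing data beyond death". The section adds that, depending on the number and balance of deaths, "principal stratification may be used to additionally estimate the survivor average causal effect".

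Section {20a} sets out the models. HMGB-1 on day 7, and ctDNA at discharge and 6 months, "will be analyzed by linear mixed-effects models, with corresponding measurements at baseline as covariates". Of these, "the one for circulating tumor DNA in blood will additionally contain a random intercept per patient, to account for the repeated outcome measurements". The rejection index, from a biopsy at 6 months, is compared by a proportional odds model stratified by center.

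The outcomes section {12} places the baseline ctDNA sample before transplantation and the baseline HMGB-1 sample at the time of transplantation. Table 1 lists both at Visit 0.

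**The concern.** A value that does not exist because the patient has died should not be imputed. A living patient who misses a blood draw, or whose baseline tube was lost, is a different case, and the stated reason does not reach it. Yet the rule covers every remaining secondary outcome, including one measured on day 7, when death can explain very little.

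Two things are at stake:

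- **Missing baseline.** With baseline as a covariate, a patient without a baseline sample leaves the model although the outcome was measured. For ctDNA, both post-transplant values go. This happens however a complete case is defined.
- **Missing 6-month ctDNA.** A model with a random intercept per patient can use a patient who has only a discharge sample. If complete case means a patient with all samples, that discharge value is lost. The discharge comparison then becomes conditional on being alive and sampled at 6 months, which may depend on outcome and on arm.

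**Working it through.** **Inputs from the sample size section {14}:** 24-month risk of recurrence or death of 15% (control) and 5% (HOPE), exponential times, 12 months of accrual plus 24 months of minimum follow-up, dropout of 5%, 220 patients in two arms of 110.

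**Step 1. Check that these rates are the ones the plan used.** HR = ln(0.95)/ln(0.85) = 0.0513/0.1625 = 0.316, which matches the stated 0.32. The Lachin-Foulkes method on the log hazard ratio, two-sided 5% and 80% power, gives 207.5 patients and 25.5 events, matching 208 and 26. Then 208/0.95 = 219, or 220 in equal arms. The plan's figures reproduce. It gives no figure for missing secondary outcomes.

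**Step 2. How much can death explain?** The risk by month t is 1 − S(24)^(t/24).

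| Time | Control | HOPE | Patients of 110 + 110 |
|---|---|---|---|
| Day 7 (t = 7/30.4375 = 0.23) | 0.16% | 0.05% | 0.17 + 0.05 = about 0.2 |
| Month 6 | 1 − 0.85^0.25 = 4.0% | 1 − 0.95^0.25 = 1.3% | 4.4 + 1.4 = about 5.8 |

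These counts include recurrences in living patients, who can still be sampled. On the planning rates they are therefore ceilings for death. Mortality early after transplantation may exceed a constant hazard, so they are a guide only.

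**Step 3. What else is expected to be missing?** Dropout is 0.05 × 220 = 11 over the whole trial. Spread evenly over 24 months (an assumption), that is 11 × 6/24 = about 3 by month 6. Missed samples and biopsies in patients who stay in the trial come on top, and the documents give no figure for them. So on these rates nearly all missing HMGB-1 values would be in living patients. At month 6 the split between dead and living cannot be fixed from the documents.

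**Step 4. Cost of a missing baseline sample.** If a fraction m of patients is dropped, the SE grows by 1/√(1 − m). The documents do not give m. For m = 5% the factor is 1/√0.95 = 1.026; for m = 10% it is 1/√0.90 = 1.054. Keeping these patients recovers only part of this loss, because their outcomes enter without baseline adjustment.

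**Step 5. Cost of a missing 6-month ctDNA sample, by reading.** A simulation compared a mixed model on all available rows with one restricted to patients who have both post-transplant samples (200 runs per scenario). It assumed 208 patients, a true effect of 0.40 SD and a within-patient correlation of 0.6.

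| Assumed loss of 6-month samples | All available rows | Only patients with both samples |
|---|---|---|
| 15%, unrelated to any value | SE 0.126, no bias | SE 0.135 (about 7% larger), no bias |
| About 9%, driven by the discharge value in the control arm only (deliberately adverse) | estimate 0.41 | estimate 0.50 |

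If a complete case is a row, the analysis is the all-rows analysis and nothing is lost.

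**The case against.** **The text never says that discharge values are deleted.** A reader might infer that complete case analysis defeats the ctDNA mixed model. The documents do not support that. Complete case is undefined, a mixed model as usually fitted drops rows and not patients, and the purpose stated for the patient intercept, "will additionally contain a random intercept per patient, to account for the repeated outcome measurements", fits the row reading. This objection stands: the deletion is one possible reading and cannot be called the plan.

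**The detail belongs in the SAP.** Section {20a} defers detailed methods to a separate SAP, which may well define a case. This stands for the definition alone. It does not remove the point, because section {20c} already fixes a rule and supports it with a reason that does not cover the living.

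**Complete case analysis is acceptable for single measurements.** HMGB-1 on day 7 and the rejection index each have one post-transplant value. If missingness depends only on variables in the model, complete cases are valid, and imputing the outcome from those same variables adds almost nothing. This stands for missing outcomes. It does not answer a missing baseline covariate, where an observed outcome is thrown away.

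**Death is already addressed.** The optional survivor average causal effect deals with truncation by death. It does so only for those who died; it says nothing about missing values in living patients.

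**Conclusion.** The point holds in a limited form. The stated reason justifies not imputing for patients who died before the time point: at most about 6 of 220 by month 6 and almost none by day 7, if the exponential planning rates apply. It does not justify the rule for living patients. Under either reading of complete case, a missing baseline HMGB-1 or ctDNA sample discards an observed outcome. Whether discharge ctDNA values are also lost depends on a definition that the article does not give.

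The size is modest and depends on missingness that the documents do not state: an SE about 5% larger if 10% of baseline samples were missing and, on the patient reading only, the losses in Step 5. The primary analysis and the sample size are untouched.

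A reader might go further in two ways that the documents do not support:

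- **A fixed share of discharge ctDNA values is lost.** Counting every event by month 6 and every dropout of the whole trial gives (5.8 + 11)/220 = 7.6%. That is a ceiling: it includes recurrences in living patients and dropouts after month 6, and it applies only on the patient reading.
- **The bias has a known direction or size.** Any such figure rests on assumed missingness. The 0.50 in Step 5 follows from a scenario chosen to be adverse.

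**What to change.** In section {20c}, and in the SAP to match:

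1. State that the ctDNA mixed model uses all available post-transplant samples, so that a missing 6-month value does not remove the discharge value.
2. Keep patients with a missing baseline HMGB-1 or ctDNA value, either by imputing the overall baseline mean (not by arm) with a missing-value indicator, or by a constrained baseline model in which the arms share a baseline mean.
3. Limit the reason against imputation to patients who died before the time point.

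Multiple imputation of the Rejection Activity Index in living patients is optional and not part of this point.

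The cost is a wording change and slightly more analysis work, with no new data. Step 2 assumes that the baseline sample is taken before any treatment effect. For HMGB-1, listed only as at the time of transplantation, the text should confirm this. The 6-month ctDNA contrast from a mixed model on all rows still extrapolates implicitly for patients who died before 6 months; the plan's optional survivor analysis is the place to address that.
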